### Discomfort or expected risk

The volunteers may experience discomfort during the casting of the dental arches and sensitivity after use of the whitening agents. This sensitivity will diminish after the cessation of treatment.

### Information and clarification

The volunteers will receive answers to any questions they may have and clarification regarding issues related to the procedures, risks, benefits and other subjects related to the study. The researchers will commit to providing updated information obtained throughout the study, even if this information could affect the volunteers’ willingness to continue participating. All volunteers will be treated at the dental clinic of the University Nove de Julho to resolve any treatment needs. The participants will also benefit esthetically from the whitening treatment.

### Procedures

The selected participants will be randomly allocated by lots to the different groups, as shown in Table 1.

**Table 1 Tab1:** **Summary of experimental conditions**

Group	Presence or absence of change in tooth color	Application site	Treatment
1	Presence	Maxillary and mandibular anterior teeth	Placebo gel without hydrogen peroxide - Formula e Açao – Sao Paulo/SP
			- without activating source
2	Presence	Maxillary and mandibular anterior teeth	6.0% hydrogen peroxide –White Class with Calcium, FGM – Joenville/SC
			- without activating source
3	Presence	Maxillary and mandibular anterior teeth	7.5% hydrogen peroxide –White Class with Calcium – FGM – Joenville/SC
			- without activating source
4	Presence	Maxillary and mandibular anterior teeth	7.5% hydrogen peroxide – Oral-B 3D White, Oral-B - EUA
			- without activating source

For each group, 16 individuals enrolled at the Dental Clinic of the University Nove de Julho will be selected. After receiving all necessary information regarding the study, including the procedures and possible risks, the volunteers who agree to participate and their respective guardians will sign a statement of informed consent.

### Tooth whitening method using 6.0% or 7.5% hydrogen peroxide gel

Castings will be made of the volunteers’ upper and lower arches and plaster will be poured into the molds. Individual plastic molds (vacuum formed, flexible acetate 1 mm in thickness) will be made for each arch using the plaster models. After fitting the molds in the oral cavity, the volunteers will receive oral and written instructions on how to use the whitening gel and will be instructed to perform proper oral hygiene with dental floss and a toothbrush prior to the application of the whitening agent. The volunteers will be instructed to use the molds with whitening gel (6.0% or 7.5%, depending on which group the volunteer is in) one hour a day for 7 days.

### Tooth whitening method using placebo gel without hydrogen peroxide

Castings will be made of the volunteers’ upper and lower arches and plaster will be poured into the molds. Individual plastic molds (vacuum formed, flexible acetate 1 mm in thickness) will be made for each arch using the plaster models. After fitting the molds in the oral cavity, the volunteers will receive oral and written instructions on how to use the whitening gel and will be instructed to perform proper oral hygiene with dental floss and a toothbrush prior to the application of the whitening agent. The volunteers will be instructed to use the molds with whitening gel one hour a day for 7 days. Then 30 days after the beginning of treatment, the volunteers in this group will receive the whitening treatment with 6.0% hydrogen peroxide gel, following the same instruction as the first gel used.

### Tooth whitening using whitening strips

The participants in this group will receive four disposable whitening strips for daily individual use. The volunteers will be instructed to perform proper oral hygiene with dental floss and a toothbrush prior to the application of the whitening strips. The volunteers will receive oral and written instructions on how to use the whitening strips, which will be placed on the surface of the teeth for 30 minutes twice a day for 7 days.

### Evaluations

Evaluations of dental sensitivity, discoloration and satisfaction with the whitening will be carried out for all groups at the following times: pre-treatment period (T1), immediately following the first treatment period (T2), after 7 days (T3), after 30 days (T4), after 6 months (T5), after 12 months (T6), after 24 months (T7) and after 48 months (T8).

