### Assessment of dental sensitivity

The volunteers will be asked to assess the degree of sensitivity at all evaluation times, using a visual analog scale. This is a numeric scale that runs from 0 (absence of sensitivity) to 10 (maximum sensitivity) [14].

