## Discussion

Tooth whitening can be performed in a dentist’s office or with the use of a home kit [3]. At-home whitening should be supervised by a dental professional and consists of the application of different concentrations of a peroxide gel (carbamide or hydrogen) to the teeth with the aid of personalized molds [9]. A number of publications have attested to the efficacy and biological safety of the at-home method [2, 10, 16]. Since the first proposal for home tooth whitening by Haywood and Heymann [9], both *in vitro* and *in situ* studies have demonstrated that whitening does not harm dental tissues and allows surprising esthetic results when properly employed [1, 17].

It is important to understand the action mechanism of the whitening agent and possible chemical interactions with dental tissues to minimize undesirable effects, such as tooth sensitivity. Hydrogen peroxide (H_2_O_2_) is the main whitening agent employed. It is a thermally unstable free radical with a low molecular weight, which penetrates the enamel and dentin through diffusion [18]. Complex molecules of organic pigments in the tissues are broken down into simpler hydrophilic molecules through an oxidation-reduction reaction by the action of perhydroxyl ions originating from the degradation of H_2_O_2_
[1]. These simpler molecules are easily removed from the dental tissue when in contact with water, thereby providing the desired whitening effect [5, 6, 16–20]. This is the action mechanism of peroxide in both the whitening process performed in the dentist’s office and the self-administered method performed in the comfort of the patient’s own home [1, 5, 6].

The concentration of the whitening agent and exposure time on the dental surfaces are important aspects to consider. Haywood and Heymann [9] proposed the home whitening of vital teeth with a 10% carbamide peroxide gel applied with the aid of molds. This protocol is still considered the gold standard for comparisons with novel methods. The main problems reported in studies involving different concentrations of carbamide peroxide (10 to 22%) are linked to the duration of use and contact between the gel and dental surfaces (an average of 6 hours, which is considered high by current standards) [1, 6, 19, 20] and the occurrence of gingival irritation and dental sensitivity during treatment [3].

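### Dental sensitivity is rated only at scheduled visits, so at most days 1 and 7 of the 7-day course carry a rating

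*Protocol article*

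**What the plan says.** The Evaluations section of the protocol article sets eight assessment times for all groups: before treatment (T1), then "immediately following the first treatment period (T2), after 7 days (T3), after 30 days (T4), after 6 months (T5), after 12 months (T6"), and finally at 24 and 48 months. The section Assessment of dental sensitivity attaches the score to these times: "The volunteers will be asked to assess the degree of sensitivity at all evaluation times, using a visual analog scale". The scale runs from 0 to 10.

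Treatment lasts a week in every group. The peroxide gels are worn "one hour a day for 7 days", the placebo gel section gives the same duration, and the strips are used "30 minutes twice a day for 7 days".

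On the expected course of the symptom, the section Discomfort or expected risk lists "sensitivity after use of the whitening agents" and adds: "This sensitivity will diminish after the cessation of treatment". The Specific objectives include analysing the increase in sensitivity in adolescents under home whitening.

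**The concern.** The article describes sensitivity as a consequence of using the agents that declines after treatment. The informative period is therefore the treatment week and the hours or days just after it. The schedule places one or two ratings there, and the rest fall weeks to years later.

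Sensitivity is part of the trial's stated aim and the main treatment-related risk that the article names for participants aged 12 to 20. If a participant has discomfort on, say, days 3 and 4 that has settled by the next rating, no scheduled score shows it. The trial could then report a lower incidence and a lower peak than participants experienced. It could say nothing about when sensitivity starts or how long it lasts.

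The early ratings also carry the whole comparison with placebo. The placebo section gives that group 6.0% peroxide gel 30 days after treatment begins, so by T5 there is no untreated comparator.

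**Working it through.** The article gives no figure for sensitivity to reproduce. Its one sample-size calculation concerns colour and has no bearing here. The check is a count of treatment days that carry a rating.

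**Inputs.** A 7-day course in every group (the three treatment-method sections); T1 to T8 (Evaluations); sensitivity scored at those times (Assessment of dental sensitivity). The first application is counted as day 1 and the last as day 7.

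**Two wordings are open.** T2 may follow the first application or the whole first course. T3 has no stated starting point for its 7 days. The possible readings are:

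| Reading | T2 | T3 | Treatment days rated | Treatment days not rated |
|---|---|---|---|---|
| a | after first application, day 1 | day 7 from start | 1 and 7 | 7 − 2 = 5 |
| b | after first application, day 1 | after the course (day 8 if counted from T2, day 14 if from the end of the course) | 1 | 7 − 1 = 6 |
| c | end of course, day 7 | 7 days later, day 14 | 7 | 7 − 1 = 6 |
| d | end of course, day 7 | day 7 from start, same day as T2 | 7 | 7 − 1 = 6 |

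Under (c) and (d) the single rating comes as the course ends. If that is not counted as during treatment, all seven days are unrated.

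**Later ratings.** T4 falls 30 − 7 = 23 days after the last application if counted from the start, or 30 days if counted from the end. T5 to T8 run from 6 to 48 months. None of these can recover what happened within the week.

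**Starting point of T4.** Counted from the start, T4 falls when the placebo group's peroxide course is due to begin (day 30). Counted from the end of the first course, it falls at 7 + 30 = day 37, about when that 7-day course would be finishing (30 + 7 = 37). The two readings give different placebo comparisons.

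**Can the share missed be estimated?** Only by assumption, and the answer depends on which one is chosen.

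- *Assumption 1:* each affected participant has one episode of d = 1, 2 or 3 consecutive days, with all seven start days equally likely. A day-7 rating catches d/7 = 14%, 29% or 43%. Ratings on days 1 and 7 catch (d + 1)/7 = 29%, 43% or 57%. The share missed is between 1 − 4/7 = 43% and 1 − 1/7 = 86%.
- *Assumption 2:* sensitivity, once begun, lasts until treatment stops. A rating at the end of the course then catches every case, and none is missed.

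The article supports neither assumption over the other, so no figure for the share missed is claimed.

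**The case against.** The strongest reply is that T2 may do the job. The placebo group has a second course, so the first treatment period most naturally means the first 7-day course, which makes T2 an end-of-course rating. The article speaks of sensitivity after use and of a decline once treatment stops. That fits a symptom that lasts while treatment continues, and T2 would then catch it before it fades. T2 minus T1 is a legitimate measure of increase. Late visits are no defect in themselves, because they also serve colour and satisfaction. A case report form might ask for the worst sensitivity since the last visit, and an article would commonly omit that wording.

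Most of this stands. It limits the loss to onset, duration and any peak or brief episode that has settled by the rating. It does not remove the loss, because the rating times are stated outright and none lies between day 1 and day 7. A recall question at T2, if there is one, would narrow the gap but would depend on memory over a week.

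Two stronger readings are tempting and are not supported:

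- A reader might infer from the Discussion's "the occurrence of gingival irritation and dental sensitivity during treatment" that the article places this trial's sensitivity within the course. That phrase describes studies of carbamide peroxide. For this trial's own agents the evidence is the risk section.
- A reader might infer that group differences are pulled toward zero, so that a product causing brief pain would look like placebo. That needs episodes to be short and over before T2, which nothing in the article establishes.

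**Conclusion.** The point holds in a limited form. Five or six of the seven treatment days carry no sensitivity rating under every reading of T2 and T3. The trial cannot describe onset, duration or an earlier peak, and incidence and peak severity may be understated. The size of any understatement cannot be derived from the article, and a bias in the group comparison is possible but not shown. The conclusion assumes that the published schedule is complete for sensitivity and that the visit score has no recall period covering the course. Separately, T2 and T3 can be read as the same day, and T4 has two possible dates. That is a wording defect whatever is decided about in-course ratings. The change is worth making but does not invalidate the trial.

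**What to change.** Have participants in all four groups record the same 0–10 score once a day on treatment days 1 to 7, as the worst sensitivity in the last 24 hours. A one-page diary can go out with the written instructions they already receive.

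Compare groups on the maximum in-course score, adjusted for T1. A responder outcome is optional. If used, it should be the proportion reaching a pre-set increase over T1, not any increase. With seven readings set against one, exchangeable continuous noise and no true effect, the chance that at least one reading exceeds T1 is 1 − 1/8 = 7/8, or 88% (less if many scores tie at zero). Such an outcome could be nearly saturated under placebo.

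Keep T2 to T4 to describe resolution. Give T2, T3 and T4 as study days, so that T2 and T3 cannot coincide and it is clear whether T4 precedes the placebo group's peroxide course.

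The cost is a diary page, a wording change, a small burden on participants and some missing diary days. No extra visit, staff or procedure is needed. Recruitment is reported as under way, so participants already treated would have no diary data. Introducing the diary in all four groups at the same time keeps the comparison among later participants fair.

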### Assessment of dental sensitivity

The volunteers will be asked to assess the degree of sensitivity at all evaluation times, using a visual analog scale. This is a numeric scale that runs from 0 (absence of sensitivity) to 10 (maximum sensitivity) [14].

### Colorimetric evaluation

The tooth color of all participants will be evaluated before and after the whitening procedures. Color readings of the vestibular region of the maxillary and mandibular anterior teeth will be performed by a previously trained examiner blinded to the allocation of the volunteers to the different groups. A digital spectrophotometer will be used for the colorimetric evaluation.

### Calculation of sample size

Considering a difference of 2.8 in *W*, 95% power, 5% error and standard deviation of 2.1 based on data from the literature [15], a minimum of 16 participants are needed for each group (see Table 1), to which 15% will be added to compensate for possible losses, totaling 19 volunteers per group. This calculation was made using the STATISTICA program.

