### Organization and statistical treatment of data

The data will be tabulated and treated with the aid of SPSS 12.0 for Windows. Descriptive analysis of the data will be performed. Either the chi-squared test or Fisher’s exact test will be used to determine associations among the categorical variables. Student’s *t*-test and analysis of variance (ANOVA) will be used to compare mean colorimetric data. Pearson’s correlation coefficients will be calculated to determine the strength of correlations among the continuous variables. The level of significance will be set at 95% (*P* <0.05).

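### The 95% power is that of one unadjusted two-group t-test, but the plan compares four products by t-test and ANOVA at P<0.05 with no control across pairs or visits

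*Protocol article*

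**What the plan says.** The Calculation of sample size section of the Protocol article gives one set of inputs: a difference of 2.8 in W, with "95% power, 5% error and standard deviation of 2.1 based on data from the literature". From these it concludes that "a minimum of 16 participants are needed for each group", "to which 15% will be added to compensate for possible losses, totaling 19 volunteers per group". It does not say which pair of groups, which visit or how many comparisons the power refers to.

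The rest of the article sets out a wider comparison:

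- Table 1 has four groups: placebo gel, 6.0% gel, 7.5% gel and 7.5% strips.
- The Specific objectives include comparing the efficacy of the gels and the strip.
- The Evaluations section assesses all groups at T1 to T8, which is one baseline and seven later visits.
- The Organization and statistical treatment of data section says that Student's t-test and "analysis of variance (ANOVA) will be used to compare mean colorimetric data", and sets one significance level, P<0.05, for everything. It names no adjustment, primary pair or primary visit.

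W appears only in the sample-size section. The Colorimetric evaluation section names no colour index.

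**The concern.** The sample-size section and the analysis section both use 5%, but for different things. In the first, 5% is the error of one comparison of two groups. In the second, it is applied to each of several t-tests and ANOVAs on four groups and up to seven visits. Four groups form six pairs, and three of these are against placebo.

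This leaves two possibilities. If the pairs are tested unadjusted, 5% is not the chance of a false claim about some product. If the pairs are adjusted, now or in a later analysis plan, 16 per group no longer gives 95% power for a pairwise difference of 2.8. In both cases the sample-size statement does not describe the pairwise analysis. At stake are how far a reported difference between products can be trusted, and whether the stated power is the power the trial has.

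**Working it through.** **Inputs.** Difference 2.8, SD 2.1, power 95%, error 5%, 16 per group and 15% for losses come from Calculation of sample size. Four equal groups come from the Abstract and Table 1. Seven post-baseline visits come from Evaluations. The sidedness of the 5% is not stated; two-sided is assumed because it reproduces the figure.

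**Step 1: the plan's own figure.** Standardised difference: 2.8/2.1 = 1.333.

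- Normal approximation: n = 2 × [2.1 × (1.960 + 1.645)/2.8]² = 14.6, so 15 per group.
- Exact t-test: noncentral t with 2n − 2 degrees of freedom and noncentrality 1.333 × √(n/2). At n = 15 the power is 94.1%, and at n = 16 it is 95.4%. The smallest n reaching 95% is 16.
- Losses: 16 × 1.15 = 18.4 and 16/0.85 = 18.8. Both round up to 19.

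So 16 and 19 are reproduced, for one two-group comparison with no adjustment.

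**Step 2: false positives at one visit, pairs unadjusted.** With no true difference and 16 per group, 50,000 simulated trials gave the following chance of at least one P<0.05:

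| Family | Simulated | If tests were independent |
|---|---|---|
| 6 pairs | 20.3% | 1 − 0.95⁶ = 26.5% |
| 3 pairs v placebo | 12.7% | 1 − 0.95³ = 14.3% |

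The simulated values are lower because pairs share groups.

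**Step 3: several visits.** The documents give no between-visit correlation, so this step rests on an assumed range. Counting all seven visits (10,000 simulated trials each):

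| Assumed correlation | 6 pairs | 3 pairs v placebo |
|---|---|---|
| 0 | 80% | 61% |
| 0.5 | 68% | 50% |
| 0.8 | 49% | 34% |

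These show direction only. The placebo group receives 6.0% gel 30 days after starting treatment, so T5 to T8 contain no true placebo comparison.

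**Step 4: power for one pair differing by 2.8, after adjustment at one visit.** Power is the probability that a noncentral t exceeds the critical value c, with noncentrality 1.333 × √(n/2): 3.77 at n = 16 and 4.11 at n = 19. Tukey and Dunnett use pooled degrees of freedom 4(n − 1), that is 60 and 72. The Dunnett critical values were simulated. Bonferroni uses two-group degrees of freedom.

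| Method | n = 16 | n = 19 |
|---|---|---|
| Tukey, 6 pairs (c = 2.643; 2.630) | 86.6% | 92.7% |
| Dunnett, 3 v placebo (c = 2.411; 2.397) | 91.0% | 95.4% |
| Bonferroni, 6 pairs | 81.9% | 89.8% |
| Bonferroni, 3 pairs | 88.4% | 93.9% |

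**Step 5: omnibus ANOVA at one visit.** Noncentral F with λ = n × Σ(mean − grand mean)²/2.1². At n = 16:

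- Means 0, 1.4, 1.4, 2.8 (least favourable): Σ = 2 × 1.4² = 3.92, λ = 14.2, power 87.9%.
- Means 0, 2.8, 2.8, 2.8: Σ = 2.1² + 3 × 0.7² = 5.88, λ = 21.3, power 97.5%.
- Means 0, 0, 2.8, 2.8: Σ = 4 × 1.4² = 7.84, λ = 28.4, power 99.6%.

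**The case against.** The strongest reply is that this is mostly missing detail. A journal article often leaves the post-hoc method and primary visit to the full protocol or analysis plan, and neither is shown. The sample-size arithmetic is correct. ANOVA, which the article names, holds 5% at a given visit. The t-test might be meant for before-and-after comparisons, and no sentence says that any significant pair at any visit counts as a finding. Even after adjustment, power stays well above 80%.

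Much of this stands, and it rules out several stronger readings that a reader might infer:

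- *That 95% power holds only for the t-test.* It does not: the omnibus ANOVA reaches 97.5% when placebo differs from three equal active groups. A significant omnibus test, though, does not say which product differs, and the objectives ask that.
- *That the trial's error rate is some stated figure such as one half or two thirds.* Such figures need an assumed decision rule and an assumed correlation. They also count visits after the placebo group has had active gel.
- *That T4 is safely placebo-controlled.* The article starts the delayed gel 30 days after the beginning of treatment and places T4 after 30 days without saying from when. Counted from the end of the 7-day course, T4 would fall near day 37.

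The reply does not remove the mismatch between two things the article does state. An unseen plan could add a correction, but then the stated 95% would no longer be true for pairwise comparisons at 16 per group.

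**Conclusion.** The concern holds in a limited form. Sixteen per group is right for one unadjusted two-sided comparison of two groups and is not an arithmetic error. The analysis as written applies the same 5% to four groups without control across pairs or visits.

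The size rests on the pairwise t-tests being run unadjusted. On that condition, the chance of at least one false positive at a single visit is about 20% (six pairs) or about 13% (three pairs against placebo). Over several visits it is higher, by an amount that depends on the between-visit correlation and on which visits count. Adjusted power for 2.8 is 87% (Tukey) or 91% (Dunnett) at 16 evaluable per group, and 93% or 95% if all 19 complete. Because 19 is the allowance for losses, 16 is the number to quote. Omnibus ANOVA power runs from 88% under the least favourable means to 97.5% and above.

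All power figures assume that the difference of 2.8 and the SD of 2.1 apply to the outcome and visit that are tested. A reader might conclude that the trial is underpowered; these figures do not support that. The point should be fixed but does not threaten the trial.

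**What to change.** Name one primary analysis in the statistical section: the change in W at one visit that is clearly placebo-controlled. T3 qualifies, since 7 days falls before the delayed gel whether counted from the start or the end of the course. T4 qualifies only if the text states that it is measured before that gel; the whitening-method section for placebo and the Evaluations section must be reconciled on this.

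Analyse by ANOVA or ANCOVA, followed by Tukey if all pairs matter or Dunnett if each active product is compared with placebo. Declare the other visits and colour indices secondary. Restate the power in the sample-size section as 87% (Tukey) or 91% (Dunnett) at 16 evaluable per group, and say which comparison it refers to.

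The cost is a change of wording, a stricter threshold for each pair and a somewhat lower stated power. No extra participants are needed. If the sponsor prefers to keep 95% after adjustment, Bonferroni would need 20 per group (three comparisons with placebo) or 23 (six pairs), before losses. The article reports that the trial is still recruiting and evaluating tooth colour, so the choice should be fixed and dated before groups are compared.

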**Methods/design:**

The aim of the proposed controlled clinical trial will be to assess colorimetric changes and increased dental sensitivity in adolescent patients submitted to tooth whitening with 6% and 7.5% hydrogen peroxide using home kits with whitening strips. Adolescents aged 12 to 20 years will be allocated to different groups based on treatment (*n* = 16 per group): (1) placebo; (2) 6.0% hydrogen peroxide (White Class with Calcium, FGM); (3) 7.5% hydrogen peroxide (White Class with Calcium, FGM); and (4) 7.5% hydrogen peroxide (Oral B 3D White, Oral-B). After the whitening procedures, the participants will be evaluated using a visual analog scale for tooth sensitivity and digital spectrophotometry to measure changes in color. Descriptive analysis of the data will be performed. Either the chi-squared test or Fisher’s exact test will be used for the determination of associations among the categorical variables. Student’s *t*-test and analysis of variance will be used to compare mean colorimetric data. Pearson’s correlation coefficients will be calculated to determine the strength of correlations among the continuous variables.

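### The enrolment target is given as 19 per group in the sample-size section but as 16 per group in the abstract and under Table 1 (76 versus 64 in total)

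*Protocol article*

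**What the plan says.** Three places in the protocol article give a number per group.

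- **Calculation of sample size.** The inputs are "95% power, 5% error", a difference of 2.8 in *W* ("Considering a difference of 2.8 in" *W*) and a "standard deviation of 2.1 based on data from the literature". They lead to a minimum of 16 per group, "to which 15% will be added to compensate for possible losses, totaling 19 volunteers per group".
- **Abstract, Methods/design.** Adolescents "will be allocated to different groups based on treatment (*n* = 16 per group").
- **Procedures, text under Table 1.** "For each group, 16 individuals enrolled at the Dental Clinic of the University Nove de Julho will be selected".

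The planned analysis of colour is Student's *t*-"test and analysis of variance (ANOVA) will be used to compare mean colorimetric data" (Organization and statistical treatment of data). The trial status section says that recruitment is under way.

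**The concern.** The sample-size section separates two quantities: the number needed for the power claim (16) and the number to recruit so that 16 remain after losses (19). The other two places describe intake, through the acts of allocating and selecting, yet they give the number needed. Neither calls its 16 an evaluable or post-loss figure.

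A reader therefore cannot tell whether the trial takes in 64 or 76 participants, or whether a final enrolment of 64 would meet the plan or fall 12 short. The power claim also depends on the answer, because 16 evaluable per group leaves no room for losses. Since recruitment is in progress, the target is already in use.

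**Working it through.** **Inputs.** Difference 2.8, SD 2.1, power 95%, error 5%, loss 15%, minimum 16 and inflated 19 per group come from the sample-size section. Four equal groups come from Table 1 and the text under it. The *t*-test comes from the statistical section. Sidedness is not stated.

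**Step 1: reproduce the 16.** The standardised difference is d = 2.8 / 2.1 = 1.333. For n per group, the two-sample *t*-test has 2n − 2 degrees of freedom and noncentrality d × √(n/2). Power is the probability that a noncentral *t* variable exceeds the 5% critical value.

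| n per group | df | noncentrality | power, two-sided 5% |
|---|---|---|---|
| 13 | 24 | 3.399 | 90.3% |
| 14 | 26 | 3.528 | 92.4% |
| 15 | 28 | 3.651 | 94.1% |
| 16 | 30 | 3.771 | 95.4% |
| 19 | 36 | 4.110 | 97.9% |

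So 16 is exactly the smallest n that reaches 95%. A one-sided 5% test reaches 95.1% at n = 13 and would have given 13 as the minimum. It does not reproduce the stated 16, so two-sided is assumed from here on.

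**Step 2: reproduce the 19.** Adding 15% gives 16 × 1.15 = 18.4. Dividing by the retained fraction gives 16 / 0.85 = 18.8. Both round up to 19.

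**Step 3: totals.** 4 × 19 = 76 and 4 × 16 = 64, a difference of 12 participants.

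**Step 4: apply the plan's own 15% loss to each intake.**

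- Intake of 19: 19 × 0.85 = 16.15, so 16 remain and power is 95.4%.
- Intake of 16: 16 × 0.85 = 13.6, so 13 to 14 remain and power is 90.3% to 92.4%. That is 95 − 92.4 = 2.6 to 95 − 90.3 = 4.7 points below the stated value.

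With an intake of 16, losing one participant per group is enough to fall below 95% (94.1% at n = 15).

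**The case against.** The sample-size section is the only place where the number is derived, and it says plainly that the allowance will be added. It also refers to Table 1 beside the 16, so the 16 printed under that table can be read as the base minimum before the allowance. On this view 19 was simply not carried through, and the power is intact. This largely stands as an explanation of how the discrepancy arose. It does not remove the discrepancy, because the abstract and the Table 1 text are worded as intake. Nor does the condensed form of an article account for it: nothing is left out here; two incompatible figures are printed.

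It is also fair to say that the consequence is modest. Even in the unfavourable case, power stays at 90% or above for a difference of 1.33 SD, and no estimate is biased.

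Three stronger readings are tempting and are not supported:

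- *The trial will enrol 16 and miss its power.* The article does not settle which number governs. The shortfall is conditional on 16.
- *Follow-up to 48 months makes damaging losses certain.* No expected loss by visit is given, and the power calculation is not tied to month 48. The placebo group is switched to 6.0% peroxide 30 days after the start, so later attrition cannot affect the untreated placebo contrast. It could affect later comparisons among the active groups.
- *The type II error doubles.* It goes from 4.6% to 7.6% at n = 14 (7.6 / 4.6 = 1.65 times) or to 9.7% at n = 13 (9.7 / 4.6 = 2.1 times). In absolute terms that is 3 to 5 points.

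**Conclusion.** The point holds as an internal inconsistency in the enrolment target: 19 per group (76) in one place, 16 per group (64) in two others, with no reconciliation. A reader might take it for an arithmetic error, but both the 16 and the 19 are computed correctly.

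If the sample-size section governs, 95% power is kept and the abstract and Table 1 text are wrong. If those two places govern, power after the planned 15% loss is about 90% to 92%.

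The power figures rest on a two-sided 5% *t*-test for one pair of groups, without adjustment for several comparisons, and on the stated difference and SD. Under a one-sided test, 13 evaluable would still give 95.1%. Under the four-group ANOVA that is also named, power depends on the pattern of means: with placebo 2.8 below three equal active groups, it is 97.5% at n = 16, 95.2% at 14 and 93.4% at 13. The contradiction between 16 and 19 does not depend on any of these choices.

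**What to change.** Make the three places agree, in one of two ways:

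1. In the abstract and in the text under Table 1, state 19 randomised per group (76 in total), with 16 evaluable per group needed for the analysis. This follows the sponsor's own calculation and keeps the 95% power claim.
2. If intake is in fact fixed at 16 per group, delete the 19 and restate the power as about 90% to 92% after 15% loss.

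In either case, add that the calculation is two-sided, if it is.

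Both are text corrections. If recruitment has been working towards 64, the first also means enrolling 12 more participants. The second needs no further recruitment but accepts a slightly lower stated power.
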